### Seven secondary endpoints are set in the ESCAPE study

2.11

1.OS, defined as the time from randomization to death from any cause.2.Each PFS in first-line treatment and second-line treatment based on RECIST v.1.1 criteria.3.Objective response rate (ORR), defined as the proportion of CR and partial response (PR) cases in total cases based on best overall response using RECIST v.1.1 criteria, and disease control rate (DCR), defined as the proportion of CR, PR, and stable disease (SD) cases in total cases in first-line and second-line treatment.4.Time to treatment failure (TTF), defined as the time from commencement of first-line therapy to earliest time of PD using RECIST v.1.1 criteria, death from any cause, or cancellation of therapy in first-line treatment.5.Total TTF from first-line to second-line treatment, defined as the time from commencement of first-line therapy to earliest time of PD using RECIST v.1.1 criteria, death from any cause, or cancellation of the therapy in second-line treatment.6.Safety in first-line and second-line treatment evaluated by Common Terminology Criteria for Adverse Events v4.0 system.7.HRQOL in first-line and second-line treatment evaluated by EORTC QTQ-C30, FKSI-DRS, and EQ-5D.

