### Definition of endpoints

2.10

The primary endpoint is total progression-free survival (PFS) from randomization to PD based on RECIST v.1.1 criteria examined with CT or MRI or death during second-line therapy. PD during first-line therapy is not counted as an event based on the definition. In case of cancellation during first-line therapy caused by severe AEs or refusal of patient without confirming PD, the end date of first-line therapy is not counted as cessation, and the case continues to receive the second-line therapy.

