### Sample size consideration and anticipated completion of enrollment

2.13

Based on the AXIS trial (second-line axitinib versus sorafenib) reported by Rini et al. [2] and the reports from Akaza et al. [11], the median total TTF would be calculated as 26.1 (10.4 + 15.7) months for combination of INFα + IL-2 and axitinib, and 15.3 months (10.5 + 4.8) for the combination of sunitinib and axitinib. In this study, hypothetical median TTFs were set for 26 months in the combination of INFα + IL-2 and axitinib and 15 months for the combination of sunitinib and axitinib. We calculated the sample size from the study duration of 5 years (two-year entry period and three-year observation period) and the difference in total TTF between the groups. To detect a significant difference between the groups by a log-rank test with significant level of 0.05 and power of 80%, at least 65 patients in each group are required. Furthermore, given the assumption that approximately 10% of randomized patients will not be evaluated for various reasons, the target sample size was set at 72 patients per group (total 144 cases).

The final patients were enrolled in September 2017, and the entire study will be completed by September 2020.

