### Planned statistical analyses

2.14

Intention-to-treat analyses in each group will be performed, and survival curves will be estimated with Kaplan-Meier method. A log-rank test will be used to evaluate differences in the survival curves between the two groups of patients. Hazard ratio will be estimated with the Cox proportional hazard model. Restricted mean survival time will be considered to quantify the treatment benefit in the absence of proportional hazard assumption in survival curves. ORR (CR + PR) and DCR (CR + PR + SD) in each group using the best response evaluated by RECIST v1.1 will be estimated for 95% confidence interval with Clopper-Pearson method. AEs in each group will be aggregated by grades and types, and the proportion of AEs will be compared between the groups by Fisher's exact test. The chronological changes in the HRQOL from the baseline evaluation using EORTC QLQ-C30, FKSI-DRS, and EQ-5D will be compared. All the tests will be two-sided, and a *P*-value of 0.05 will be considered statistically significant.

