Each ORR of axitinib as second-line after sunitinib as first-line and after cytokine as first-line treatment was 11.3% and 32.5%, and each PFS was 4.8 months and 12 months in the AXIS trial, respectively. Therefore, axitinib was more effective after cytokine than after sunitinib [2]. Escudier et al. reported that each ORR of sorafenib 800 mg as second-line after disease progression using cytokine as first-line and sorafenib 1200 mg as second-line after disease progression using sorafenib 800 mg as first-line treatment was 20% and 5.2%, respectively. Namely, sorafenib was more effective after cytokine than dose escalation [24]. Moroto et al. reported that each excellent ORR and DCR of sorafenib after 6- or 12-week administration of combination of IFNα and IL-2 was 44.4% and 94.4%, respectively [25].

In some cases of mRCC, especially in Japanese patients whose response to cytokine therapy would be good, the duration of response by the first-line cytokine and second-line TKI could be longer than that of first-line TKI treatment and second-line treatment with another agent. Conversely, AEs of sunitinib in Japanese patients tend to be more severe than in Westerners; therefore, management for the AEs of sunitinib is sometimes difficult, even though we had accumulated experience of AEs with sunitinib. To improve the outcome of sequential treatment for mRCC, we planned a prospective randomized controlled open-label trial between first-line IFNα + IL-2 and second-line axitinib and first-line sunitinib and second-line axitinib, which is considered as a standard first- and second-line treatment for patients with mRCC with favorable risk. Our expectation of this trial is it will clarify better first- and second-line sequential treatment for mRCC, especially in patients with favorable risk and some patients with intermediate risk. In doing so, the results of the trial will definitely contribute to new information for the strategy of first- and second-line sequential treatment for patients with mRCC.

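### TTF and total TTF are timed from the start of first-line therapy, which does not fit the declared intention-to-treat analysis; both should be timed from randomisation

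*Protocol article*

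**What the plan says.** Four time-to-event endpoints in the protocol article have a stated origin.

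- Primary endpoint (section 2.10): "The primary endpoint is total progression-free survival (PFS) from randomization to PD", or death, during second-line therapy.
- OS (section 2.11, item 1): "OS, defined as the time from randomization to death from any cause".
- First-line TTF (section 2.11, item 4): "Time to treatment failure (TTF), defined as the time from commencement of first-line therapy to earliest time of PD", death, or cancellation of first-line therapy.
- Total TTF (section 2.11, item 5): "Total TTF from first-line to second-line treatment, defined as the time from commencement of first-line therapy to earliest time of PD", death, or cancellation of therapy in the second line.

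Section 2.14 states the analysis principle once, for everything: "Intention-to-treat analyses in each group will be performed". It makes no exception for the TTF endpoints. The Discussion confirms the lack of blinding: "we planned a prospective randomized controlled open-label trial". Section 2.13 sizes the trial on total TTF ("hypothetical median TTFs were set for 26 months in the combination of INFα + IL-2 and axitinib and 15 months" for the sunitinib sequence) and allows that "approximately 10% of randomized patients will not be evaluated for various reasons".

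**The concern.** An intention-to-treat comparison needs a time zero that every randomised patient has. Commencement of therapy is not one. A patient who is allocated and then withdraws before the first dose has no TTF or total TTF as these are defined. A patient who withdraws just after the first dose is an early first-line failure, because cancellation is a TTF event. Two patients who differ by a day are thus treated quite differently.

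Allocation is known before the first dose, and the arms differ in burden (injected cytokines against an oral drug). Not starting, or starting late, could therefore depend on the arm. If it does, the TTF comparison is between groups selected after randomisation. The total PFS and total TTF curves would also run on different clocks.

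**Working it through.** **1. Definitions side by side.**

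| Endpoint | Time zero | Defined for a never-starter? |
|---|---|---|
| Total PFS (primary) | Randomisation | Yes |
| OS | Randomisation | Yes |
| First-line TTF | Start of first-line therapy | No |
| Total TTF | Start of first-line therapy | No |

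Once one patient fails to start, the last two rows cannot be met together with the intention-to-treat statement.

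**2. The plan's own sample size.** Inputs from section 2.13: medians 26 and 15 months, 24 months of entry plus 36 of observation, significance level 0.05 and power 80%. Section 2.14 makes tests two-sided. Exponential survival and uniform entry are my assumptions.

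- Hazard ratio = 15/26 = 0.577.
- Schoenfeld events = 4 × (1.960 + 0.842)² / (ln 0.577)² = 103.8, so 104.
- Event probability, with λ = ln 2 / median, A = 24 and F = 36: 1 − [exp(−λF) − exp(−λ(A+F))]/(Aλ). This gives 0.886 (median 15) and 0.717 (median 26), mean 0.801.
- Patients per group = 104 / 0.801 / 2 = 64.9, so 65. The plan's figure reproduces.
- Allowance: 65 × 1.1 = 71.5 or 65 / 0.9 = 72.2, consistent with the stated 72.

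**3. Power for total TTF if never-starters are left out.** The article gives no never-start rate, so a range is assumed. Power = Φ(√(events/4) × |ln 0.577| − 1.960).

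| Left out, both arms | Patients | Events | Power |
|---|---|---|---|
| 0% | 144 | 115 | 84.0% |
| 2% | 141 | 113 | 83.3% |
| 5% | 137 | 110 | 82.1% |
| 10% | 130 | 104 | 80.0% |

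Leaving out 10% of the cytokine arm only gives 82.2%. With the actual entry period of 48 months (section 2.7) and 36 months of further follow-up, 72 per group gives 123 events and 86%, and 65 per group gives 111 events and 83%. Precision is not at stake.

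**4. Possible bias.** If a fraction x of an arm fails at time zero and the rest follow an exponential curve with median m, the arm's median is (m / ln 2) × ln[(1 − x)/0.5].

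| x | m = 15 | m = 26 |
|---|---|---|
| 0% | 15.0 | 26.0 |
| 5% | 13.9 | 24.1 |
| 10% | 12.7 | 22.0 |

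For total TTF these shifts apply only if the never-starters receive neither line, so they are an upper illustration. What matters is imbalance. With x = 10% in the cytokine arm and 0% in the sunitinib arm, the first-dose analysis would still show 26 against 15, a gap of 11 months. From randomisation it would be 22.0 against 15, a gap of 7.0. With the imbalance reversed it would be 26 against 12.7, a gap of 13.3. The direction therefore depends on which arm has more never-starters, and the article does not say.

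**The case against.** **Exclusion is not stated.** No section says that never-starters are left out, intention-to-treat points the other way, and a SAP that is not shown could supply a rule. That is fair as to what the sponsor will do, and I do not claim that patients will be dropped. But the point is not a missing rule. The article states both the time origin and the analysis principle, and the two conflict; a later rule would have to override the published definition.

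**Timing treatment failure from first dose is a coherent choice.** It is, for a description of treated patients. It should then be labelled as such rather than placed under intention-to-treat.

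**Stronger readings that the article does not support.**

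- A reader might take the 10% in section 2.13 as the expected share of never-starters, or about 7 of 72 per arm. It is a general allowance for patients not evaluated, for unspecified reasons.
- A reader might infer that refusal will differ between an injected and an oral regimen. That is plausible in an open-label trial, but no rate by arm is given.
- A reader might count every never-starter as an immediate failure on both endpoints. That fits first-line TTF. It does not fit total TTF, whose cancellation event lies in second-line treatment. Section 2.10 follows similar logic for the primary endpoint: cancellation of first-line therapy without PD does not end the sequence. That passage concerns stopping rather than never starting, but a patient who skips first-line therapy and takes axitinib is likewise not a day-one total-TTF failure.
- A reader might let the use of total TTF in the sample size raise the weight of this point. That total TTF, and not the primary endpoint, was used for sizing is a separate matter.

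**Conclusion.** The point holds in a limited form. TTF and total TTF, as defined, have no time zero for a randomised patient who never starts first-line therapy, and they ignore any arm-dependent delay before the first dose. They therefore conflict with the declared intention-to-treat analysis and do not preserve the randomised comparison in this open-label trial.

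The size of the bias cannot be determined from the article. It is nil if everyone starts promptly. An assumed 10% imbalance could move the apparent difference in median total TTF by several months in either direction, and then only if those patients receive neither line. That illustration rests on exponential survival at the plan's medians. Power stays at about 80% or more throughout the range examined. The primary endpoint and OS are unaffected, so this concerns two secondary endpoints and not the main conclusion.

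**What to change.** - Time both TTF and total TTF from randomisation, and analyse all randomised patients as allocated.
- First-line TTF: count a patient who never starts first-line therapy as a failure at randomisation.
- Total TTF: keep the event definition in section 2.11 (PD, death or cancellation in second-line treatment). Follow a never-starter who proceeds to axitinib to that event. Count a patient who receives neither line as a failure at randomisation.
- Keep a version timed from first dose in treated patients, if wanted, as a labelled sensitivity analysis.
- Report by arm the number of never-starters and the time from randomisation to first dose, so that readers can judge whether the choice matters.

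Cost: two definitions are reworded and a rule for never-starters is added. Randomisation dates must already be held for OS and total PFS, and the sample size does not change. TTF lengthens by the gap between randomisation and first dose, and becomes slightly less comparable with TTF reported elsewhere in treated patients.

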### One exploratory endpoint is set in the ESCAPE study

2.12

1.Applied medicine, PFS, ORR, and DCR in third-line and fourth-line treatment.

### Sample size consideration and anticipated completion of enrollment

2.13

Based on the AXIS trial (second-line axitinib versus sorafenib) reported by Rini et al. [2] and the reports from Akaza et al. [11], the median total TTF would be calculated as 26.1 (10.4 + 15.7) months for combination of INFα + IL-2 and axitinib, and 15.3 months (10.5 + 4.8) for the combination of sunitinib and axitinib. In this study, hypothetical median TTFs were set for 26 months in the combination of INFα + IL-2 and axitinib and 15 months for the combination of sunitinib and axitinib. We calculated the sample size from the study duration of 5 years (two-year entry period and three-year observation period) and the difference in total TTF between the groups. To detect a significant difference between the groups by a log-rank test with significant level of 0.05 and power of 80%, at least 65 patients in each group are required. Furthermore, given the assumption that approximately 10% of randomized patients will not be evaluated for various reasons, the target sample size was set at 72 patients per group (total 144 cases).

The final patients were enrolled in September 2017, and the entire study will be completed by September 2020.

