Reported response rate (RR: CR + PR) of IFNα or IL-2 monotherapy was about 10%–20% [16]. United States Food and Drug Administration approved IL-2 as high dose IL-2 (600,000–700,000 IU/kg x 5 days in a two-week cycle); however, the dose of 70,000–210,000 IU/kg/day IL-2 approved in Japan was low [17,18]. Koreth et al. reported in 2011 that the administration of one million IU/day induced IL-2 regulatory T cell (Treg) for 2–3 months and controlled the occurrence of graft versus host disease (GVHD) [19]. The usual administration dose of 1.05 million IU/day for IL-2 would contribute to reinforcement of activity of natural killer cells (NK) and lymphokine activated killer cells (LAK). However, it could induce Treg and possibly reduce the antitumor effect such as NK or LAK activity. It has been reported that IFNα suppresses Treg [20]; therefore, the combination therapy of low dose IFNα and IL-2 would contribute to antitumor activity without reduction caused by Treg. Akaza et al. reported that the combination therapy of IFNα and low dose IL-2 for 42 cases of mRCC resulted in approximately 35% ORR, two cases of CR, approximately 70% DCR, 10.4 months PFS, and approximately 70% 3-year OS. These results were favorable compared with IFNα or IL-2 monotherapy [11]. The main AEs with combination therapy were fever and general malaise, which were controllable using medicines such as antipyretics. Ito et al. reported that Japanese patients with mRCC could live longer than patients in western countries undergoing IFNα therapy. Using the genetic analysis of Japanese patients, patients were able to achieve long-term survival with a good response of IFNα against mRCC [21]. Based on these reports, cytokine therapy may contribute to long-term survival for some patients with mRCC, especially Japanese patients. In fact, Naito et al. reported excellent clinical outcomes for patient with mRCC in Japan during the cytokine treatment era compared with the outcomes from the reports in western countries [7,22]. Chow et al. reported that IL-2 treatment for mRCC showed 48.1% ORR and 21.6% CR among selected patients with favorable pathology based on constitution of histological growth pattern [23]. Cytokine therapies have the potential to achieve complete and durable response for a limited group of patients with mRCC; therefore, cytokine therapy might be a selectable option as first-line treatment especially for Japanese patients with mRCC with favorable risk criteria.

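### Section 2.13 plans the cytokine–axitinib arm on 15.7 months of second-line axitinib where the Discussion gives 12, so the stated 80% power rests on an unreconciled input

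*Protocol article*

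**What the plan says.** Section 2.13 (Sample size consideration) adds a first-line and a second-line median in each arm. For cytokines then axitinib, "the median total TTF would be calculated as 26.1 (10.4 + 15.7) months". For the control sequence it gives "15.3 months (10.5 + 4.8) for the combination of sunitinib and axitinib". These are rounded for planning: "hypothetical median TTFs were set for 26 months in the combination of INFα + IL-2 and axitinib and 15 months" for sunitinib then axitinib. The section names two sources, the AXIS trial of second-line axitinib and the reports on IFNα plus low-dose IL-2. With a log-rank test at 0.05, 80% power, two years of entry and three of observation, it arrives at 65 per group, raised to 72 for about 10% not evaluable.

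The Discussion gives figures for the same components. For the cytokine combination it reports "approximately 70% DCR, 10.4 months PFS, and approximately 70% 3-year OS". For second-line axitinib, after sunitinib and after cytokines in that order, it says "each PFS was 4.8 months and 12 months in the AXIS trial, respectively".

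**The concern.** Three of the four components can be compared with the Discussion. The 10.4 months for first-line cytokines and the 4.8 months for axitinib after sunitinib agree with it. The 15.7 months for axitinib after cytokines does not: the Discussion has 12, and 15.7 appears nowhere else in the article. No other population, endpoint or source is given for it.

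The gap of 3.7 months favours the experimental arm and feeds directly into the hypothesised effect, the 65 per group and the 80% power. If 15.7 cannot be supported, a non-significant result would be read against a power that the article's own figures do not bear out.

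**Working it through.** **Inputs.** From Section 2.13: medians 26 and 15 months (from 26.1 and 15.3), entry A = 24 months, observation F = 36 months, power 80%, 65 then 72 per group. From Section 2.14: two-sided 0.05. From the Discussion: 12 months for axitinib after cytokines. From Section 2.7: actual recruitment October 2013 to September 2017, so A = 48 months; with completion by September 2020, F stays at 36.

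**Formulas.** Exponential total time with λ = ln 2 / median, so HR = control median / cytokine median. Schoenfeld events d = 4(1.960 + 0.842)² / (ln HR)² = 31.4 / (ln HR)². Event probability with uniform entry p = 1 − [e^(−λF) − e^(−λ(F+A))] / (λA). Power = Φ(√d × |ln HR| / 2 − 1.96), with d the expected events.

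**Reproducing the plan (26 versus 15).** HR = 15/26 = 0.577 and ln HR = −0.550, so d = 103.8. Event probabilities are 0.717 and 0.886, mean 0.801. Then 103.8 / 0.801 / 2 = 64.75, or 65 per group, as stated. At 65 per group 104.2 events are expected and power is 80.2%.

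**Replacing only 15.7 by 12.** The cytokine-arm median becomes 10.4 + 12 = 22.4 months. It is compared with the rounded control median, 15, and with the unrounded one, 15.3.

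| Medians (months) | HR | Events for 80% | Per group for 80% (A = 24) | Power, 65 per group (A = 24) | Power, 72 per group (A = 24) | Power, 72 per group (A = 48) |
|---|---|---|---|---|---|---|
| 26 v 15 (plan) | 0.577 | 104 | 65 | 80.2% | 84.0% | 86.2% |
| 22.4 v 15 | 0.670 | 195 | 118 | 54.7% | 59.0% | 61.5% |
| 22.4 v 15.3 | 0.683 | 216 | 131 | 50.5% | 54.7% | 57.1% |

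Example for 22.4 v 15 at 65 per group: mean event probability (0.768 + 0.886)/2 = 0.827, so 130 × 0.827 = 107.5 events, and √107.5 × 0.401/2 − 1.96 = 0.119, giving Φ = 0.547. The 22.4 v 15 row changes one input only; the 22.4 v 15.3 row also removes the rounding of the control median.

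**Sensitivity to the model.** Total time was also simulated as the sum of two independent exponential lines with the component medians, every patient going on to axitinib. At 65 per group with 24 + 36 months, power was about 97% with 15.7 and 81% with 12. At 72 per group with 48 + 36 months it was about 99% and 86 to 87%. Under this model the medians of the totals are about 31.3 months (15.7), 27.1 (12) and 18.0 (control), because the median of a sum is not the sum of the medians. It is therefore a different model from the one that gives 65.

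**The case against.** The strongest reply is that 10.4 + 15.7 = 26.1 is correct addition, the 65 follows from it, and the article calls the medians hypothetical. That stands: this is an unreconciled input, not a miscalculation.

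A second reply is that 15.7 may come from a subgroup or an endpoint that the article does not name, since Section 2.13 speaks of TTF and the Discussion of PFS. This stands in part. A change of endpoint alone would not explain a longer time: Section 2.11 adds cancellation of therapy to progression and death, so in the same patients TTF cannot exceed PFS. But the article does not establish that the patients are the same. A reader might infer that 12 is right and 15.7 wrong; the document does not show that. If another source was used for this arm only, the two arms were planned on unlike sources, and that too needs stating.

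Third, absence from the Discussion is not itself an error. The 10.5 months for first-line sunitinib is not repeated there either; the Discussion quotes 11 months from the sunitinib trial. That is fair, and the point rests on the conflict with 12, not on 15.7 being mentioned once. Using 11 would raise the control median and not restore power.

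Fourth, a reader might conclude that the trial had only even odds of success. That holds only under exponential total time. The two-stage model with full uptake still gives 80% or more with 12 months. Full uptake is the favourable end, since the Introduction says fewer patients can be treated at each successive line. With an assumed 70% uptake, a figure not in the article, the two-stage power at 65 per group is about 79% with 15.7 and 51 to 53% with 12.

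Finally, enrolment is closed and the planned analyses do not depend on planning power. This limits the remedy to the text.

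**Conclusion.** The point holds as an internal contradiction in the input that fixes the hypothesised effect. The 80% power at 65 per group is supported only if 15.7 months is, and the article's own figure for axitinib after cytokines in its named source is 12.

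By the method that reproduces 65, using 12 lowers power from 80% to between 50 and 55% at 65 per group. At 72 per group it falls from 84% to 55 to 59% with the planned entry period, and from 86% to 57 to 62% with the actual one. Reaching 80% would have needed about 118 to 131 evaluable patients per group. These figures assume exponential total time, medians that add across lines and, in the 72-per-group figures, no loss from the 72.

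The existence of the loss is firm and its size is not. The two-stage model with full uptake puts power at 81 to 87% with 12 months, against 97 to 99% with 15.7. The contradiction should be resolved before the results are interpreted.

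**What to change.** Keep the calculation made before recruitment on record as the design basis; do not rewrite the historical hypothesis. Add to Section 2.13 the source, population and endpoint of 15.7, and take the after-sunitinib figure from that same source; or acknowledge that the AXIS figure after cytokines is 12 months, as the Discussion has it.

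If 15.7 cannot be supported, state that under 22.4 versus 15 to 15.3 months the 144 patients give about 55 to 62% power by the plan's method, with the two-stage result as a sensitivity analysis and its uptake assumption declared. A null result should then be read from the hazard ratio and its interval, not against a nominal 80%.

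The cost is one reworded paragraph and possibly a less favourable stated power. No patients, visits, data or planned analyses change.

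### Section 2.13 states medians, power and sample size for total TTF, a secondary endpoint; none is stated for the primary endpoint, total PFS, and the article's own PFS figures do not support 26 versus 15 months

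*Protocol article*

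**What the plan says.** Section 2.10 of the protocol article names the primary endpoint: "The primary endpoint is total progression-free survival (PFS) from randomization to PD" or death during second-line therapy. It adds that "PD during first-line therapy is not counted as an event based on the definition".

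Section 2.11 lists total TTF as the fifth of seven secondary endpoints: "Total TTF from first-line to second-line treatment, defined as the time from commencement of first-line therapy". Besides PD and death, it counts cancellation of second-line therapy as an event. Total TTF therefore differs from total PFS in its starting point and in one event type.

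Section 2.13 sizes the trial on the planned duration "and the difference in total TTF between the groups". It sums 10.4 + 15.7 = 26.1 months for cytokines then axitinib, and 10.5 + 4.8 = 15.3 months for sunitinib then axitinib. It calls both sums total TTF and sets the hypothetical medians at 26 and 15 months. With a log-rank test, a level of 0.05, 80% power, two years of entry and three of observation, it requires 65 per group, raised to 72 for about 10% not evaluable.

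The Discussion gives some of the same figures another name. For interferon alfa with low-dose IL-2 it reports "approximately 70% DCR, 10.4 months PFS, and approximately 70% 3-year OS". For second-line axitinib after sunitinib and after cytokines, in that order, it says "each PFS was 4.8 months and 12 months in the AXIS trial, respectively".

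**The concern.** The power statement and the primary endpoint do not refer to the same variable. The term TTF is used for the source sums, for the hypothetical medians and for the difference to be detected, so it is not one stray word. The article gives no median, hazard ratio, event count or power for total PFS, and does not say that total TTF stands in for it.

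This matters for reading the result. If the primary log-rank test is not significant, readers will ask what difference in total PFS the trial could have detected, and the article gives no answer. Borrowing the 80% means assuming that 26 and 15 months describe total PFS, and one component of the 26 conflicts with a PFS figure given elsewhere in the article.

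**Working it through.** **Inputs.** Section 2.13: medians 26 and 15 months, level 0.05, power 80%, entry 24 months, observation 36 months, 65 per group before and 72 after allowance for non-evaluable patients. Section 2.14: two-sided tests. Discussion: PFS 10.4 months (cytokines), 12 months (axitinib after cytokines), 4.8 months (axitinib after sunitinib). Section 2.13 only: 10.5 months for first-line sunitinib and 15.7 months for axitinib after cytokines. Assumptions: exponential survival, uniform entry, equal allocation and no loss to follow-up.

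**Formulas.**
- Hazard ratio: HR = control median / experimental median.
- Required events (Schoenfeld): D = 4 × (1.960 + 0.842)² / (ln HR)², where 4 × (1.960 + 0.842)² ≈ 31.4.
- Event probability with λ = ln 2 / median: p = 1 − [exp(−36λ) − exp(−60λ)] / (24λ).
- Power: Φ(√D/2 × |ln HR| − 1.960), with D = n per group × (p₁ + p₂).

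**Step 1: reproduce the stated figure.**
- HR = 15/26 = 0.577 and ln HR = −0.550.
- D = 31.4 / 0.550² = 103.8, so 104 events.
- Event probabilities are 0.717 (26 months) and 0.886 (15 months), mean 0.801.
- Patients per group = 104 / (2 × 0.801) = 64.9, so 65.
- At 65 per group, 104.2 events are expected, and power is Φ(2.807 − 1.960) = 80%.

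The stated 65 is correct for the stated inputs. The arithmetic is sound; the open question is which endpoint the inputs describe.

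**Step 2: which inputs are PFS?**

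| Component | Section 2.13 (called TTF) | Discussion (called PFS) |
|---|---|---|
| Cytokines, first line | 10.4 | 10.4 |
| Axitinib after cytokines | 15.7 | 12 |
| Sunitinib, first line | 10.5 | 11 (cited trial against interferon alfa) |
| Axitinib after sunitinib | 4.8 | 4.8 |

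Two of the four agree exactly with figures reported as PFS. The 15.7 does not: it exceeds the PFS given for the same setting by 3.7 months.

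**Step 3: use the 12 months and keep the other three inputs.** The protocol's own method of adding medians is followed.
- Cytokine sequence 10.4 + 12 = 22.4 months; sunitinib sequence 10.5 + 4.8 = 15.3 months.
- HR = 15.3/22.4 = 0.683 and ln HR = −0.381.
- Event probabilities are 0.768 and 0.881.
- At 65 per group: D = 65 × 1.649 = 107.2; power = Φ(1.973 − 1.960) = Φ(0.013) = 51%.
- At 72 per group: D = 72 × 1.649 = 118.7; power = Φ(2.077 − 1.960) = Φ(0.117) = 55%.
- For 80% power: D = 31.4 / 0.381² ≈ 216 events, or about 132 per group before any allowance.

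**Step 4: how much comes from the 15.7?** The unrounded sums of section 2.13, 26.1 and 15.3 months, give HR 0.586 and 78% power at 65 per group. Replacing 15.7 by 12, with everything else held, lowers this to 51%. Almost all of the fall from 80% is due to that one input.

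**The case against.** The strongest reply is that TTF is a labelling slip. Two of the four components are PFS medians by the article's own account, and the calculation reproduces exactly. If the sponsor confirms that 26 and 15 months were meant for total PFS, the 80% and the 65 per group stand numerically and only a word is wrong. That is a fair reading and cannot be excluded. It does not dispose of the point, because the 15.7 months is nowhere called PFS and disagrees with the 12 months that is. Changing the label alone would move the conflict into the primary endpoint's power statement.

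Three stronger readings are tempting and should not be drawn.

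- A reader might infer that the article leaves open which endpoint decides the trial. It does not: section 2.10 names total PFS as primary and section 2.11 lists total TTF as secondary.
- A reader might infer that the primary test is proven to have less than 80% power. It is not: with true total PFS medians of 26 and 15 months, it has 80% under the assumptions above.
- A reader might argue that cancellations dilute the treatment contrast and so reduce power. That would concern total TTF, the secondary endpoint. The article gives no cancellation rate for either sequence from which to size it.

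The difference in starting point, randomization against commencement of therapy, is real, but the article gives no delay from which to judge its size.

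**Conclusion.** The point holds as an inconsistency between sections 2.10, 2.11 and 2.13. The stated medians, 80% power and 65 per group belong by name to a secondary endpoint, and nothing equivalent is stated for the primary one. The 80% can be carried over to total PFS only if 26 and 15 months are justified as total PFS medians, and the article's own figures do not justify them.

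The size depends on the disputed input. Power for total PFS is 80% at 65 per group if 26 versus 15 months holds, and about 51% (55% at 72) if the Discussion's 12 months replaces 15.7. These figures assume exponential survival, no loss to follow-up, medians added as in section 2.13, and 24 + 36 months. Under the four-year recruitment of section 2.7 followed by 36 months, the lower figures become 53% and 57%, so longer entry does not close the gap. The 51% is a consequence of figures in the article, not a forecast.

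**What to change.** Rewrite section 2.13 for total PFS:

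1. State the assumed total PFS median for each sequence, with the source of each component.
2. State the required number of events and the resulting power for the primary log-rank test.
3. Reconcile the 15.7 months in section 2.13 with the 12 months in the Discussion. If they are different quantities or come from different populations, say so and say which applies to total PFS. Do not simply relabel 15.7 as PFS.
4. If the PFS figures do not support 26 versus 15 months, restate the power for the enrolled size instead of keeping 80%.

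The cost is a paragraph of text and a short calculation. Enrolment closed in September 2017, so the sample size cannot change. The primary endpoint, the log-rank test and the two-sided 0.05 level need no change. The correction should be made before the final analysis; the article expects the study to be completed by September 2020.
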